#### Study processes

Seven to 20 weeks before the invitation date, the included citizens in study arms 1 and 2 will receive a link to the baseline questionnaire via their digital mail (with remote printing for exempted citizens). Questionnaire reminders will be sent out after two weeks. Instead of a second questionnaire reminder, non-respondents will be contacted via telephone after four weeks and invited to fill out the questionnaire via telephone interview. In a pilot study, the response rates among lower educational attainment and medium/higher educational attainment citizens using an invitation and a two-week reminder were assessed at 27% and 55%, respectively. The response rates increased to 40% and 64%, respectively, in the two groups, by using telephone interviews. Accordingly, we expect telephone interviews to help reach more of the lower educational attainment citizens. Questionnaire respondents will also be asked for consent to the obtaining and analysis of screening data (date of invitation, reminder, receipt of test in laboratory, and test result) from the screening program database.

Citizens who respond to the questionnaire and give consent to the use of registry data will be randomly allocated into study arms 1 and 2. Allocation will be performed in the ratio 1:1 and will use a computer-generated algorithm for randomization, based on a simple randomization procedure. Randomization will be conducted based on the study participants’ record-ID numbers. Participants will not be able to change study arm after allocation and there will be no blinding.

Citizens who take up screening within 45 days after the screening invitation and citizens with medium or higher educational attainment (i.e. 10 years or more of education) will be excluded from the analyses after randomization. This might cause attrition bias. However, randomization will be conducted externally before screening uptake is known. Furthermore, educational attainment will not be available to researchers at an individual level, unless data are pseudonymized. However, educational level and screening uptake within 45 days of invitation is not expected to be associated with study arm and, hence, no attrition bias is expected.

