#### Secondary outcomes

The 16-item decisional conflict scale [37] will be used to measure decisional conflict, i.e. uncertainty about making the right choice. It comprises five subscales, including the decisional support subscale and the (perceived) effectiveness of the decision subscale. Scores range from 0 to 100 and data are collected at follow-up.

Worry about CRC will be assessed using three items on worry about CRC. Two items assess worry and anxiety when considering CRC screening and one assesses worry about the result of a screening test. Items have also been developed by the authors based on literature searches [19, 20, 38–40]. Scores are in the range of 3–15. Assessments are made at baseline and follow-up.

Health literacy is a multidimensional measure of a person’s ability to access, understand, appraise, and apply information about healthcare, disease prevention, and health promotion [41]. It will be measured at baseline using the 16-item HLS-EU-Q16 scale [41].

The use of the decision aid will be measured among citizens receiving an invitation to use it. However, detailed process data will not be collected, since the primary aim of this trial is to investigate the effectiveness of having the decision aid provided, regardless of actually reading it. Usability and acceptability have been further assessed in the development phase of the decision aid [26].

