#### Questionnaires

Three different questionnaires will be administered in this trial: the baseline (knowledge, seven items; attitudes, four items [34]; worry, three items; health literacy – HLS-EU-Q16, 16 items [41, 44]) and follow-up (knowledge; attitudes; worry; decisional conflict, 16 items [37]) questionnaires, and the questionnaire for the historic study arm participants (knowledge; attitudes; worry; health literacy; decisional conflict) (Fig. 2).

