### Statistical methods

All statistical analyses will be carried out in Stata/SE 14 (STATACorp LP, College Station, TX, USA). Analyses will be carried out on a 5% significance level, stratified to gender. Estimates will be presented with 95% confidence intervals. Intention-to-treat analyses will be conducted.

Pearson’s chi-square test will be used to test differences in demographic characteristics between respondents and non-respondents as well as between those included in each study arm with lower educational attainment, in order to test for baseline differences. Furthermore, differences in educational attainment and screening uptake within 45 days in each study arm will be compared in order to evaluate the risk of attrition bias.

The main outcome of the trial is informed choice. Informed choice is difficult to measure and the evaluation will be based on adequate knowledge about CRC screening and consistency between attitudes towards CRC screening and screening uptake. This will be judged at group level not individual level. [46] Differences in distributions of responses to knowledge, attitudes, uptake, decisional conflict, and worries in the study arms will be analyzed using the independent sample t-test for continuous variables and Pearson’s chi-square test for categorical variables. The relative risk (RR) will be estimated for uptake using a logistic regression analysis with study arm 2 as the reference comparing to both study arm 1 and the historic cohort. Citizens are defined as having taken up CRC screening if they returned a stool sample within three months after the screening invitation was sent out [47]. For the numeric scale outcomes, a linear regression analysis will be conducted to compare the means between study arms 1 and 2 and study arm 2 and the historic cohort, using study arm 2 as the reference. For ordinal scales, not normally distributed as assessed by histograms and qq-plots, ordinal regression analyses will be conducted, estimating odds ratios for higher scores in study arm 1 and the historic cohort as compared to study arm 2, using study arm 2 as the reference.

Further, generalized linear models from the binary family will be conducted to test if socioeconomic variables (including health literacy) modify the effectiveness of the decision aid on knowledge, attitudes, and uptake. *P* values for these analyses will be estimated using the Wald test.

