### Power calculations

The smallest difference between outcomes between groups is expected to be found in attitudes estimates (a 14% difference in proportions having a positive attitude towards screening [19]) Based on this assumption, power calculations (considering a 5% significance level and an 80% statistical power) indicate that we need to include 200 citizens with lower educational attainment in each group. We expect 47% of citizens invited to CRC screening not to return a stool sample within 45 days. Further, we know that 26% of the population has lower educational attainment [49]. By combining mailed invitations and reminders with telephone calls, we aim to reach a response rate of at least 60% for baseline questionnaire and 80% for follow-up (i.e. study participants). Further, we expect a 50% response rate in the historic study arm. In order to be able to make gender stratified analyses, and considering the rate of screening reminder, rate of lower educational attainment, and questionnaire response rate, we need to include 5000 citizens in each study arm.

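### Uptake and decisional conflict are compared between arms 1 and 2 without the baseline scores already collected: a valid analysis, but probably less precise than it could be

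*Protocol article*

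**What the plan says.** All places are in the protocol article.

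- **Timing of the scores.** Under Study processes, "Citizens who respond to the questionnaire and give consent to the use of registry data will be randomly allocated" to arms 1 and 2. The baseline questionnaire therefore precedes allocation. Under Questionnaires it contains "knowledge, seven items; attitudes, four items", plus worry and health literacy.
- **Outcomes without a baseline.** Table 1 lists uptake and decisional conflict at follow-up only. For the decisional conflict scale, "Scores range from 0 to 100 and data are collected at follow-up". Knowledge, attitudes and worry, by contrast, have planned change scores.
- **Planned comparison.** Statistical methods names the t-test and the chi-square test, then regression models. For uptake, "The relative risk (RR) will be estimated for uptake using a logistic regression analysis with study arm 2 as the reference". Numeric scales get linear regression, or ordinal regression if not normally distributed. Study arm is the only model term named, and analyses are stratified by gender.
- **Other use of a baseline score.** Health literacy enters models that test whether it modifies the effect on knowledge, attitudes and uptake. Decisional conflict is not covered, and no adjusted estimate of the arm effect is described. Table 1 nevertheless lists health literacy under a heading that includes confounders.

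**The concern.** When an outcome has its own baseline value, a change score or baseline adjustment can recover some precision. Uptake and decisional conflict have none, so only other pre-randomization predictors can help. Attitude is a plausible predictor of uptake on the protocol's own logic, because it judges informed choice partly by whether attitudes and uptake agree. Knowledge and health literacy are plausible predictors of decisional conflict.

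Precision matters here. Uptake is a binary element of the primary outcome, analysed in a few hundred citizens per arm and planned within gender strata. Randomization is simple, so nothing in the design balances the baseline scores.

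**Working it through.** **1. The plan's own sample size.** The inputs from Power calculations are "considering a 5% significance level and an 80% statistical power" and "a 14% difference in proportions having a positive attitude towards screening". The two proportions are not given. Taking 0.43 versus 0.57 (assumed, centred on 50%) with a two-sided test:

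n = [1.96·√(2·0.5·0.5) + 0.8416·√(0.43·0.57 + 0.57·0.43)]² / 0.14² = (1.386 + 0.589)² / 0.0196 ≈ 199.0, or 200 per group after rounding up.

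This reproduces the statement that "we need to include 200 citizens with lower educational attainment in each group".

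**2. Citizens expected in the analysis.** The article says "we need to include 5000 citizens in each study arm". Its rates are 60% baseline response, 80% follow-up response, 26% lower educational attainment and 47% with no sample by day 45:

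5000 × 0.60 × 0.80 × 0.26 × 0.47 = 293 per arm, or about 147 per gender per arm if split equally (assumed).

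**3. Decisional conflict.** If the baseline scores explain a share R² of the variance, the residual variance is multiplied by (1 − R²). An effect with 80% power unadjusted then has power Φ(2.80/√(1 − R²) − 1.96), and n citizens act like n/(1 − R²). R² is assumed.

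| Assumed R² | Power | Citizens needed instead of 200 | 147 act like |
|---|---|---|---|
| 0 | 80% | 200 | 147 |
| 0.05 | 82% | 190 | 155 |
| 0.10 | 84% | 180 | 163 |
| 0.20 | 88% | 160 | 184 |
| 0.25 | 90% | 150 | 196 |

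Correlations of 0.3 to 0.5 correspond to R² of 0.09 to 0.25.

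**4. Uptake.** Simulations compared arm-only logistic regression with logistic regression plus one standard-normal baseline covariate. In the adjusted analysis the relative risk was obtained by standardization. Uptake levels and covariate strength are assumed.

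With 200 per arm and uptake of 25% versus 37% (2000 runs per setting):

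| Log-odds slope per SD | Approx. R² | Power, arm only | Power, adjusted | SE ratio, log RR |
|---|---|---|---|---|
| 0 | 0 | 74.6% | 74.7% | 1.00 |
| 0.35 | 0.02 | 75.6% | 77.0% | 0.98 |
| 0.70 | 0.08 | 73.7% | 78.1% | 0.97 |
| 1.00 | 0.15 | 74.7% | 81.1% | 0.92 |

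With 294 per arm, uptake of 25% versus 35% and odds ratios per SD of 1.5, 2.0 and 2.5 (3000 runs each), power rises from 75.7 to 76.6%, 74.9 to 79.0% and 75.9 to 81.3%. The variance of the log relative risk is 1.04, 1.08 and 1.15 times larger without adjustment.

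With 293 per arm and 25% versus 37%, unadjusted power is already 88 to 89%. The gains are then smaller: 0.6, 2.1 and 4.6 points at slopes 0.35, 0.70 and 1.00.

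**5. Room for four covariates in one gender stratum.** At 25% and 37% uptake, 147 × 0.25 + 147 × 0.37 ≈ 91 events. With five slopes (arm and four covariates), that is about 18 events per slope, so the proposed model is not overloaded.

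**The case against.** The strongest case against is that this is an efficiency preference read from silence. A covariate list is usual content for an analysis plan that is not shown. The text never says that covariates are excluded, and an unadjusted comparison of randomized arms is legitimate. Part of this stands: nothing here is an error of validity. But the t-test and chi-square test are unadjusted by construction, and the regression models are described with arm as their only term. The only models that use health literacy answer a different question and leave out decisional conflict. The article therefore does state an analysis choice, and a more precise one is available.

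Other objections stand as limits on size:

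- No document gives a correlation between any baseline score and either outcome. The analysis excludes citizens who return a sample within 45 days, which may weaken the link between attitude and uptake.
- The simulations used a single covariate and pooled arms. None was run at 147 per arm.
- Questionnaire items may be missing, and health literacy cannot be scored with more than three items missing. The scores therefore exist for nearly all randomized citizens, not every one.

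A reader might also infer that chance imbalance in baseline attitude would pass for a treatment effect. The documents do not support that reading. The unadjusted confidence interval already allows for chance imbalance, and Table 1 plans baseline comparisons of attitude and knowledge between arms 1 and 2, so an imbalance would be seen.

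**Conclusion.** The point holds as a probable loss of efficiency. Adjustment would add roughly 1 to 6 percentage points of power for uptake. It would reduce residual variance for decisional conflict by about 5 to 25%. Both ranges rest on assumed prognostic strength and, for uptake, on assumed uptake levels. If the scores are not prognostic, the gain is nil.

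Two stronger readings are not supported. The planned comparison is not biased. Nor do the documents show that precision is certainly lost, because they never establish that the scores predict these outcomes. The change is still worth making: the data will already be in hand, the expected loss from adjusting is negligible, and the covariates must be fixed before outcomes are seen. The gain applies only to arm 1 versus arm 2.

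**What to change.** In Statistical methods, prespecify that the arm 1 versus arm 2 estimates for uptake and decisional conflict are adjusted for baseline attitude, baseline knowledge, health literacy and age.

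- Fit these models separately from the comparison with the historic cohort, which answers its only questionnaire after the invitation and has no pre-invitation scores.
- For uptake, average the predicted risks under each arm over the analysed citizens and report their ratio. This keeps the target a marginal relative risk. The arm coefficient of an adjusted logistic model would instead give a conditional odds ratio.
- Use simple imputation for missing attitude and health literacy scores. The missingness precedes randomization, so this is adequate. Missing knowledge items are already scored as wrong.
- Keep the unadjusted results as supportive.

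The cost is a short addition to the text and slightly more analysis work: a separate model, the standardization step and the imputation. No new data or citizens are needed.

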### Outcomes

The outcomes assessed in this trial are presented in Table 1.

**Table 1 Tab1:** Trial outcomes

Outcome	Characteristics	Assessment time	Comparisons^a^	Null Hypothesis^a^
Primary outcome (Informed choice elements)				
Knowledge	Numeric scale	Baseline	1 vs. 2	No difference
	Numeric scale	Dif_Follow-up-baseline_^b^	1 vs. 2	1 > 2
	Numeric scale	Follow-up	1 vs. 2 vs H	1 > 2 and 1 > H
Attitudes	Numeric scale	Baseline	1 vs. 2	No difference
	Numeric scale	Dif_Follow-up-baseline_^b^	1 vs. 2	No difference
Uptake	Dichotomous	Follow-up	1 vs. 2 vs H	1 > 2 and 1 > H
Secondary outcomes				
Decisional conflict	Numeric scale	Follow-up	1 vs. 2 vs H	1 < 2 and 1 < H
Worry	Numeric scale	Baseline	1 vs. 2 vs H	No difference
	Numeric scale	Dif_Follow-up-Baseline_^b^	1 vs 2	1 < 2
Effect modifiers and confounders				
Health literacy	Numeric scale	Baseline	1 vs. 2 vs. H	No difference
Background data				
Family income	Categorical	Post survey	1 vs. 2 vs. H	No difference
Occupation	Categorical	Post survey	1 vs. 2 vs. H	No difference
Marital status	Dichotomous	Post survey	1 vs. 2 vs. H	No difference
Ethnicity	Categorical	Post survey	1 vs. 2 vs. H	No difference

*H* historic study arm

^a^Group 1 refers to the intervention group and group 2 refers to the control group

^b^Dif_Follow-up-Baseline_: The mean increase or decrease in knowledge, attitude, and worry-score from baseline to follow-up will be estimated. Means will be compared between the two study arms

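### Contrasts with the non-randomised historic cohort are specified by group only; the confounder and background variables listed for all three groups have no adjusting role

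*Protocol article*

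**What the plan says.** The Study design section introduces the historic cohort so that the effect of answering a baseline questionnaire can be assessed. Table 1 then goes further. It states directional hypotheses against H for knowledge at follow-up and uptake (primary) and for decisional conflict (secondary).

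The Statistical methods section gives the analyses. Outcome distributions "will be analyzed using the independent sample t-test for continuous variables and Pearson’s chi-square test for categorical variables". Uptake is analysed "using a logistic regression analysis with study arm 2 as the reference comparing to both study arm 1 and the historic cohort". Numeric scales get a "linear regression analysis will be conducted to compare the means between study arms 1 and 2 and study arm 2 and the historic cohort", and non-normal ordinal scales get an ordinal regression with the same reference group. The only stated control of composition is gender: "Analyses will be carried out on a 5% significance level, stratified to gender".

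Table 1 has a block headed "Effect modifiers and confounders", which contains health literacy. A separate block, Background data, contains family income, occupation, marital status and ethnicity. All five are listed for comparison across 1 vs 2 vs H. In the Statistical methods section, demographic differences are tested by chi-square. The only models that use the socioeconomic variables and health literacy are those "to test if socioeconomic variables (including health literacy) modify the effectiveness of the decision aid on knowledge, attitudes, and uptake".

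**The concern.** A group-only model is right for arm 1 against arm 2, because randomisation balances composition in expectation. Nothing does that for H, yet the regressions for numeric scales, uptake and ordinal scales treat both contrasts alike. A variable listed as a possible confounder is measured in all three groups and then used only to look for effect modification. If the balance tests show that H differs, the text provides no consequence, and a balance test does not remove bias.

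Two conclusions depend on this. Arm 2 against H is the only check on the questionnaire effect. The Table 1 hypotheses against H would present a crude, non-randomised difference in the same table as the randomised result.

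**Working it through.** **1. How the groups differ (Abstract, Study processes, Study population, Power calculations).**

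| Feature | Arms 1 and 2 | Historic cohort |
|---|---|---|
| Birth month | December | October |
| Invitation period | October–December 2017 | January–March 2017 |
| Stated age | 53–74 (Abstract: 50–74) | 50–74 |
| Response path | baseline before invitation (60%), then follow-up (80%) | one questionnaire after invitation (50%) |
| Outcome questionnaire | about day 90 | 6–8 months (Abstract: 6–9) |
| Day-45 returners | excluded | not stated in the text |

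The expected overall response is similar: 0.60 × 0.80 = 48% in the arms and 50% in H. The paths differ, however. The arms must answer before invitation and again afterwards; H answers once, after its decision. The pilot shows that response depends on social position: 40% with lower against 64% with medium or higher education, even with telephone contact.

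**2. The plan's own sample size.** A 14-point difference at 80% power and two-sided 5% (sidedness assumed) gives 200 per group at 43% vs 57%, and 196 at 50% vs 64%. The stated 200 therefore reproduces near a 50% base rate. The present point does not rest on it.

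**3. Expected numbers analysed.**
- Per trial arm: 5000 × 0.60 × 0.47 × 0.26 × 0.80 = 293.
- H without the day-45 restriction: 5000 × 0.50 × 0.26 = 650.
- H with it: 650 × 0.47 = 305.5.

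**4. Precision of arm 2 vs H on a proportion near 50% (assumed), genders combined.** Half-width = 1.96 × √(0.25/n₂ + 0.25/n_H).
- n_H = 650: 1.96 × √(0.25/293 + 0.25/650) = 6.9 points.
- n_H = 305.5: 8.0 points.
- Within one gender, assuming an equal split, multiply by √2: 9.8 and 11.3 points.

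**5. Illustrative bias.** For one binary characteristic, bias = (difference in its share between groups) × (outcome difference it carries). The document gives neither factor. Assumed ranges of 5 to 20 points and 10 to 30 points give:
- low: 0.05 × 0.10 = 0.5 points;
- middle: 0.10 × 0.20 = 2 points;
- high: 0.20 × 0.30 = 6 points.

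With SE = half-width/1.96, the chance that a nominal 5% test rejects a true null is 1 − Φ(1.96 − bias/SE) + Φ(−1.96 − bias/SE).

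| Bias | n_H ≈ 306 | n_H = 650 |
|---|---|---|
| 0.5 points | 5.2% | 5.2% |
| 2 points | 7.8% | 8.8% |
| 6 points | 31% | 40% |

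The low end is harmless and the high end is not. The bias does not shrink as the sample grows.

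**6. Is the age gap real?** Under the Setting section, citizens turning 50 during the round that began in 2014 are invited just before that birthday. An October-born citizen aged 50–52 on 1 August 2017 turned 50 in October 2014, 2015 or 2016, and so was due an invitation before January 2017. If that rule was followed, those actually invited in January–March 2017 are 53 or older, as in the trial arms. If it was not, and ages are uniform, at most 3/25 = 12% of H lies outside the arms' range.

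**7. Why the day-45 restriction matters for uptake.** Let u be the share of day-45 non-returners who return by day 90 (not given). Uptake is u in a trial arm. In an unrestricted H it would be 0.53 + 0.47u, where 0.53 = 1 − 0.47. The difference with no effect of anything is 0.53(1 − u): 47.7 points at u = 10% and 31.8 points at u = 40% (both assumed, and 47% is the figure for all invited citizens). No covariate adjustment would repair this.

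**The case against.** The strongest objection is that silence is not a decision. The article never says that the H contrasts are unadjusted, it condenses a fuller document, and a covariate list is commonly left to an analysis plan that is not shown. A reader might infer that adjustment was considered and rejected; the document does not support that. What stands is narrower: the text does assign the collected variables a role, and that role is effect modification, while t-tests and chi-square tests cannot adjust. That is a badly fixed method rather than an omitted detail.

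Four further stronger readings also fail:
- *The plan names five confounders.* Only health literacy is under that heading; income, occupation, marital status and ethnicity are background data.
- *H is demonstrably younger.* Step 6 shows that the stated ranges may be only a labelling difference.
- *The H results are known to be biased by several points.* All samples come from the same register, region and residence date, and differ mainly by birth month, which gives no evident reason for large social differences. The 0.5 to 6 points are assumed, and most of that range is below the sampling half-width.
- *H includes early returners, so its uptake contrast is invalid.* The text does not say either way, and the participant flow chart is not visible here.

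It is also fair that H is auxiliary, that the regressions give no direct arm 1 vs H contrast, and that covariates cannot cure calendar period or questionnaire timing. These points limit what adjustment achieves. They do not make the crude contrast the better main estimate.

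**Conclusion.** The concern holds in limited form. As written, the comparisons with H rest on group-only methods within gender strata, although variables suited to confounding control are planned for all three groups. Differences in who responds can therefore pass as a questionnaire effect (arm 2 vs H) or, for the 1 > H hypotheses, as a mixture that also includes the decision aid.

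The size is unknown. The figures in step 5 show only that bias could range from negligible to close to the sampling half-width under assumed confounder strengths. The arm 1 vs arm 2 comparison is not affected. The change is worth making because it is cheap and because Table 1 attaches primary and secondary hypotheses to H.

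**What to change.** In the Statistical methods section, leave arm 1 vs arm 2 as planned. For every contrast with H:

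1. Restrict H to the age range of the trial arms and, for uptake, to citizens who had not returned a sample by day 45. State both restrictions explicitly.
2. Make the main estimate a regression or standardised estimate adjusted for age, family income, occupation, marital status and ethnicity, within gender strata.
3. Report two sensitivity analyses: the crude estimate, and a version that adds health literacy. Keep health literacy out of the main model because H reports it 6–8 months after invitation and after its screening decision.
4. State here and in Table 1 that contrasts with H are observational, and that differences in calendar period and questionnaire timing remain uncorrected.

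**Cost.** No new data collection: the background variables are registry data listed for all three groups, H's questionnaire includes health literacy, the samples are drawn on age, and 90-day uptake already requires invitation and return dates. The analysis work grows slightly. H shrinks from about 650 to about 305 under the day-45 restriction (half-width 6.9 to 8.0 points). If a full 12% were also lost on age, H would be about 305.5 × 0.88 = 269 and the half-width 1.96 × √(0.25/293 + 0.25/269) = 8.3 points. Citizens with more than three missing health literacy items drop out of one sensitivity model only.

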#### Primary outcome

Informed choice will be evaluated based on the following primary outcomes: consistency of knowledge about CRC screening, attitudes towards CRC screening, and screening uptake [34].

Knowledge will be measured via questionnaire before and after intervention using a seven-item scale developed by the authors based on both a literature search and patient information needs as previously clarified in focus group interviews [25]. Post-intervention levels and changes from baseline to follow-up will be evaluated.

Screening attitudes will be estimated using the translated four-item attitudes scale, ranging from 4 to 28 points [34]. The scale has been translated into Danish from English with conventional forward-backward translation [35]. Attitudes will be assessed at baseline and at follow-up.

Data on screening uptake will be collected from the CRC screening program database. Citizens will be defined as having taken up CRC screening if they return a stool sample within three months (90 days) after the screening invitation has been sent out [36].

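### Effect modification on knowledge and attitudes is assigned to a binary-family model, although the plan defines and analyses both as numeric scales

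*Protocol article*

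**What the plan says.** Under Primary outcome, attitudes are measured on a "translated four-item attitudes scale, ranging from 4 to 28 points", and knowledge is measured "using a seven-item scale developed by the authors". Table 1 gives both the type numeric scale and gives uptake the type dichotomous. For attitudes, the only comparison of arms 1 and 2 after the intervention in Table 1 is the change from baseline. For knowledge there is both a change and a follow-up level. The table footnote says: "The mean increase or decrease in knowledge, attitude, and worry-score from baseline to follow-up will be estimated".

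For the main effect, Statistical methods states: "For the numeric scale outcomes, a linear regression analysis will be conducted to compare the means between study arms 1 and 2". It adds ordinal regression with odds ratios for ordinal scales that are not normally distributed. The last paragraph of the section then turns to effect modification: "generalized linear models from the binary family will be conducted to test if socioeconomic variables (including health literacy) modify the effectiveness", and the effect in question is "the effectiveness of the decision aid on knowledge, attitudes, and uptake". P "values for these analyses will be estimated using the Wald test".

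Two other statements touch on proportions. Statistical methods describes the main outcome partly in terms of adequate knowledge, and Power calculations sizes the trial on a 14% difference in the proportion with a positive attitude. Neither gives a threshold.

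**The concern.** One model family is assigned to three outcomes, and it suits only one of them as the plan defines them. Two consequences follow if knowledge and attitudes are cut to fit the model.

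First, the target changes. The main analysis compares means (or odds of a higher score, under the ordinal fallback), while the modifier analysis would compare the probability of lying above a cut. An interaction on one of these scales need not exist on the other, so the test would not show whether the reported main effect varies with income, occupation or health literacy.

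Second, cutting a numeric score discards information in interaction tests, which usually need more information than the main effect does.

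**Working it through.** **1. Does the model fit each outcome?** Binary family is read here as the binomial (Bernoulli) family.

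- Uptake, yes or no: fits.
- Attitude score, 4 to 28: not a binary response.
- Attitude change: possible range 4 − 28 = −24 to 28 − 4 = +24. It can be negative and is not a binary response.
- Knowledge change: with one point per item (assumed), −7 to +7. Same conclusion.
- Knowledge at follow-up: if scored as the number correct out of seven, a grouped binomial can take it without a cut. The section on missing data makes this scoring plausible, since don't-know and missing answers count as wrong. The text does not say that this model is meant.

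**2. Change of target.** An illustration with assumed values: the decision aid shifts a normal score by 0.353 SD in two subgroups alike, so there is no interaction on the mean scale.

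- Subgroup with 50% above the cut in the control arm: Φ(0 + 0.353) = 63.8%, a difference of 13.8 points.
- Subgroup with 80% above the cut: Φ(0.842 + 0.353) = 88.4%, a difference of 8.4 points.
- Relative risks: 63.8/50 = 1.28 and 88.4/80 = 1.10.

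The cut alone produces apparent modification on the difference and ratio scales.

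**3. Information kept after a cut.** For a normal score cut at c with a proportion p on one side, relative efficiency is φ(c)² / [p(1 − p)].

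- Median cut: 0.3989² / 0.25 = 2/π = 0.637, a loss of about 36%. The sample would need to be 1/0.637 = 1.57 times as large to compensate.
- 80:20 cut: 0.490, a loss of about 51%, factor 2.04.

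**4. The plan's own sample size.** Base rates are not stated. With 57% against 43% (assumed), two-sided 5%, 80% power and pooled variance:

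n = [1.960·√(2·0.5·0.5) + 0.842·√(0.57·0.43 + 0.43·0.57)]² / 0.14² = 199.04, rounded up to 200 per group. This matches the stated 200, which is a main-effect figure.

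**5. Expected yield, from Power calculations.** 5000 × 0.60 × 0.47 × 0.26 × 0.80 = 293 per arm, or about 147 per arm in each gender. With the 40% response that the pilot reached among lower educational attainment citizens in place of 60%, the yield is 195 per arm.

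**6. Interaction power, as illustration only.** Assumptions: a modifier split 50:50, an interaction as large as the design's main effect (14 points with rates near 50%, or d = z(0.57) − z(0.43) = 0.353 SD), and two-sided 5%. With n per arm there are n/2 per cell:

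- numeric: power = Φ(0.353 / √(4/(n/2)) − 1.96)
- binary: power = Φ(0.14 / √(4·0.25/(n/2)) − 1.96)

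| n per arm | Score kept numeric | Score cut |
|---|---|---|
| 293 | 57% | 40% |
| 200 | 42% | 29% |
| 147 (one gender) | 33% | 22% |

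A simulation of 2,000 runs per setting, linear model against binomial-logit Wald test, gave 57% against 40% at 293 per arm with a median cut, and 55% against 30% with 80% of scores on one side of the cut.

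**The case against.** The strongest case on the other side has four parts.

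- **A cut is not forced.** Follow-up knowledge can be a grouped binomial, and a bounded attitude score can be rescaled to 0–1 and fitted as a fractional response. It would therefore be too strong to infer that the plan must dichotomise both scales. This stands. But the article states neither reading, and either would still put the modifier test on a different scale from the linear main-effect model.
- **Proportion versions are already in the design.** The power calculation uses a proportion with a positive attitude, and the main outcome refers to adequate knowledge. If those were meant, only the cut-points are absent, and an article may leave these to the analysis plan. This stands too: the missing cut-points are not the error. But a cut-point in the analysis plan would settle only where to cut. The mismatch with the numeric outcomes in Table 1, the change of target and the loss of information would remain.
- **The main-effect model is not always linear.** Where the ordinal fallback applies, the main effect is itself an odds ratio. This is correct, and the remedy has to follow whichever model is used.
- **The size of the loss depends on assumptions.** A reader might infer that the documents show the interaction tests to be underpowered, or that a third of the sample is lost. They do not: no interaction power is stated, neither normality nor a median cut is given, and the power figures above rest on assumed rates, modifier split and interaction size.

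**Conclusion.** The point holds as an inconsistency between the model named for effect modification and the plan's own definition and main analysis of knowledge and attitudes. It is clearest for the raw attitude score and for the change scores, and weakest for follow-up knowledge.

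If the scales are cut, the modifier tests answer a different question from the main effect. They also lose about 36% of the information under a median split of a roughly normal score, and more under an uneven split. Under the assumptions stated, that is about 17 points of power at 293 per arm and about 10 points at 147.

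These are supplementary analyses. A reader should not infer that the primary comparison of arms or the sample size is affected; neither depends on the modifier models. The change should be made, but the trial's main result does not hang on it.

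**What to change.** For knowledge and attitudes, test arm-by-modifier terms in the model used for the main effect of the same outcome: the linear model, or the ordinal model where that fallback applies. Keep the binomial-family model for uptake only. The Wald test can stay as stated.

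Adjustment for the baseline score is optional. If it is added, it should enter the main-effect model as well, so that both refer to the same quantity.

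If a proportion version or a grouped binomial is really intended for either scale, say so, with the cut-points and the reason for them fixed before the data are seen, and state that the modifier analysis then targets a different quantity from the main effect.

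The cost is one or two sentences in the analysis plan. No extra data, questionnaires or participants are needed.
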